### Concomitant

Drugs out of curative plan such as heat-clearing and detoxicating traditional Chinese medicine and oral or intravenous hormone that maybe affect the effect of Oseltamivir shall not be used. When taking antipyretic and analgesic drugs necessarily, the usage and dosage of antipyretic and analgesic drugs are recorded as one of the secondary efficacy evaluation indicators. Concomitant medication is required due to adverse events during the trial, which should be recorded in the CRF in detail.

### Follow-up

All included patients will be re-evaluated after five days of treatment to assess the efficacy and safety. Patients whose symptoms worsened will receive a supply of relevant medicine and a written withdrawal schedule.

### Outcomes

By searching for relevant literature [26–28] and interviewing relevant clinical experts, we observed the efficacy from five dimension: temperature, symptoms, use of antipyretic analgesics, etiological test and inflammatory factor test.

### Primary outcome measure

Time of temperature recovery.

Definition: time when axillary temperature drops below 37.3℃ without repetition after the first use of the drug.Regulation of axillary temperature recording (Mercury thermometer and body temperature measuring instrument): after the first usage in 24 h, the temperature will be measured in the first 2 h, 4 h, 6 and 8 h; and after 24 h, the temperature will be measured at least 2 times a day. When axillary temperature drops below 37.3℃ without repetition in 24 h, it is the treatment end point.

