Fever, occurring in 95% of influenza children, is the most salient sign, 59% of children 3 years has fever 39.0℃ [9]. Fever outdoes all others and is the only reliable predictor of influenza virus infection [10]. We selected time of temperature recovery as the primary measure to evaluate treatment effect. Time when fever begins to subside is also included as a secondary outcome to observe when RDN starts to work. Apart from fever suddenly, clinical features of ILI such as cough, chills, running nose, sore throat, headache, myalgia and so on are common clinical manifestations [9, 11, 12]. So clinical symptom record table and score of each symptom are developed to record time and degree of disease alleviation to understand the change of disease. The disappearance rate of individual symptoms will be recorded after medication to evaluate RDN’s effect on each symptom. Although clinical manifestations are typical for diagnosis, laboratory testing is necessary too [13]. So we select rapid antigen test [14] to estimate negative conversion rate of influenza viral and detect its type [2]. Special circumstance such as symptomatic treatment needs to be considered, thus we will record number and frequency of antipyretic and analgesic drugs if using. Children < 5 years are likely to develop severe complications (age < 2 years easier) [15], hence we will monitor incidence of complications of influenza to ensure children’s safety.

Reduning (RDN), consisting of Qing Hao (*sweet wormwood herb*), Zhi Zi (*fructus gardeniae*) and Jin Yin Hua (*honeysuckle*), is a traditional Chinese medicine injection under patent protection (Chinese patent number CN201711264903.0). RDN treats influenza virus through alleviating pulmonary inflammation and reducing inflammatory factors release [16]. Meanwhile RDN has been recommended to treat H7N9 influenza infection [17]. A case of 108 patients of influenza in adult, RDN has a comparable effect with Oseltamivir but faster work and short course [18]. We intend to evaluate efficacy and safety of RDN to provide a possible therapeutic strategy for influenza in children. Oseltamivir (Kewei) is the recommended drug for influenza in children approved by *Influenza Diagnosis and Treatment Program (2018 Edition)* [15] and *Recommendations for Prevention and Control of Influenza in Children (2016–2017)* [19], so we choose it as positive control to reflect the superior curative efficacy and safety of RDN objectively.

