### Secondary Outcome measure

In clinical manifestation, we will record such as time point of fever subside, time point of disease alleviate, degree of disease remission and disappearance rate of individual symptoms;In laboratory examination, we will record the rate of negative conversion of Influenza viral;In treatment, we will record the usage and frequency of antipyretic and analgesic drugs;In outcome, we will record the incidence of complications of influenza.

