### Analysis contents

List the frequency of cases enrolled, violated and dropped out;List the details of cases of violation, dropout, low compliance, time-window violation, out of protocol drug usage.List the datasets for analysis.Comparability analysis: compare demographic data and other baseline indicators to measure the balance of each group.Effectiveness analysis: FAS and PPS analysis. The study is a multi-center clinical trial, the influence of central effect on efficacy indicators should be considered in the analysis. Measurement data uses covariance analysis which considering the central factor, and count data uses CMH test corrected by the central stratification.Safety analysis: compare the incidence of AE in each group and describe the AE in the trial. Compare the changes of normal/abnormal laboratory indicators before and after the test, and list the details of cases with abnormal/abnormal aggravation before and after the test.Concomitant medication analysis: compare the details of each group and list them down.

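### Recovery is scored from the thermometer alone while antipyretics are permitted, so antipyretic use can bring the counted recovery time forward and mainly dilute the treatment difference

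*Protocol article*

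**What the plan says.** Under Primary outcome measure, time of temperature recovery is the "time when axillary temperature drops below 37.3℃ without repetition after the first use of the drug". Required readings are at 2, 4, 6 and 8 h after the first dose; then "after 24 h, the temperature will be measured at least 2 times a day". The section ends: "When axillary temperature drops below 37.3℃ without repetition in 24 h, it is the treatment end point". Table 2 adds a temperature check at each 24 h visit up to 120 h.

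Under Concomitant, antipyretic and analgesic drugs may be taken when necessary, and "the usage and dosage of antipyretic and analgesic drugs are recorded as one of the secondary efficacy evaluation indicators". Secondary Outcome measure repeats this: "In treatment, we will record the usage and frequency of antipyretic and analgesic drugs". The Introduction shows that the authors had symptomatic treatment in mind: "Special circumstance such as symptomatic treatment needs to be considered, thus we will record number and frequency of antipyretic and analgesic drugs if using".

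Under Analysis contents, the only adjustment named for continuous outcomes is for centre: "Measurement data uses covariance analysis which considering the central factor". Concomitant medication is compared and listed separately. Nowhere does the article say how a reading taken under antipyretic cover counts toward the primary endpoint.

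**The concern.** Every child enters with a temperature above 38℃, and antipyretics act directly on the quantity that defines recovery. A child whose fever is suppressed by an antipyretic and a child whose illness has resolved can give the same readings and so the same recovery time. The Introduction presents temperature recovery as the measure of treatment effect, yet the scored time reflects study drug and antipyretic together.

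This would matter little if antipyretic use were the same in both arms. The plan's own premises make that hard to assume. It lists antipyretic use among its efficacy outcomes, so it expects treatment might change it, and its planning figures have fever lasting longer on oseltamivir than on RDN. Longer fever gives more occasion for antipyretics. What is at stake is the size and the meaning of the primary treatment difference.

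**Working it through.** **1. What the 24 h rule catches.** Take three courses after a dose of antipyretic:

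- One dose, a dip below 37.3℃, and a rebound at a scheduled reading: not counted as recovery. The rule works.
- A dip, then a rebound between readings: counted. No reading is required from 8 h to 24 h, a gap of 24 − 8 = 16 h. After 24 h two readings a day suffice, about 24/2 = 12 h apart if evenly spaced, and no spacing is set.
- Repeated doses that keep the readings below 37.3℃: counted, however often the child is measured.

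As an example of the minimum schedule, suppose the first reading below 37.3℃ is at 8 h. The confirming period runs to 8 + 24 = 32 h. The 24 h visit in Table 2 may be the only required reading inside it, if both readings of the second day are taken after 32 h.

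There is a milder case too. A child close to recovery who takes one antipyretic dose can cross 37.3℃ a few hours early and stay below it. The recovery is real, but its counted time is brought forward.

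**2. Direction.** The Sample size section plans on 46.50 h for oseltamivir and 30.47 h for RDN, a difference of 46.50 − 30.47 = 16.03 h. If antipyretic use follows fever, the oseltamivir arm uses more, more of its recovery times are brought forward, and the difference shrinks.

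**3. Size, by illustration.** The plan has no figure of its own on this point to reproduce, and gives no rate of antipyretic use. Both inputs below are assumptions:

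- d = difference between arms in the share of children scored early because of antipyretics
- s = hours by which each of these children is scored early
- shift in the mean difference = d × s

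| d | s (h) | Shift (h) | Planned 16.03 h becomes (h) |
|---|---|---|---|
| 0.10 | 12 | 1.2 | 14.83 |
| 0.10 | 24 | 2.4 | 13.63 |
| 0.20 | 12 | 2.4 | 13.63 |
| 0.20 | 24 | 4.8 | 11.23 |

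The last column assumes more use in the oseltamivir arm. The shift is 1.2/16.03 = 7% to 4.8/16.03 = 30% of the planning difference. A wider range of d = 0.05–0.30 and s = 4–24 h gives 0.05 × 4 = 0.2 h to 0.30 × 24 = 7.2 h.

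**4. Effect on the test.** Take the stated SDs at face value: 1.74 and 1.69 h, pooled √((1.74² + 1.69²)/2) = 1.715 h. With 100 per group, power against a zero difference stays near 100% even after a 7.2 h shift (16.03 − 7.2 = 8.83 h left). On the plan's own figures, the exposure is in the estimate rather than in a test against zero.

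**The case against.** Four objections carry weight.

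- **Counting recovery regardless of antipyretic use is a recognised treatment-policy choice.** This stands. The current definition is not wrong in itself, but the article does not declare that choice.
- **A condensed article may leave such detail to the full protocol or analysis plan.** This stands in part. Sensitivity analyses and case report form layout may well be there. The endpoint definition, however, is set out here with its threshold, measurement times and confirmation rule, and for symptomatic treatment the article offers only recording.
- **Protection exists.** A recorded rebound cancels a dip, two readings a day is a minimum, Table 2 adds daily checks, and the Discontinuation section has a 24 h check after early stopping. This limits the problem without removing it, because none of it addresses repeated dosing.
- **Blinding.** The double-dummy design limits antipyretic use driven by knowledge of the allocation. It does not limit use driven by a different course of fever.

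A reader might infer that the bias could equally well favour RDN. The documents do not support that: inflation would need more antipyretic use in the arm with shorter fever, and they give no reason to expect it.

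A reader might also note that 100 per group is reproduced if 15.35 h is read as a superiority margin. With two-sided 0.05 and an assumed 80% power, n = 2 × (1.960 + 0.842)² × 1.715²/(16.03 − 15.35)² = 100. On that reading a 0.4 h shift would cut power from about 80% to 21%. But the article states no power and does not say that the final test is made against 15.35 h, so this collapse cannot be claimed.

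**Conclusion.** The point holds in a limited form. As written, the plan can count antipyretic-suppressed fever as recovery, or date a true recovery too early, and the 24 h rule only partly prevents this. The main expected consequence is a diluted difference, on the assumption that the arm with longer fever uses more antipyretics.

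The size is unknown. The 1.2–4.8 h range rests wholly on the assumed 10–20 point imbalance and 12–24 h advance; it shows that the effect could be material, not that it will be. It would also be too strong to call the endpoint invalid. The gap is that its meaning under antipyretic use is undeclared and that no antipyretic-aware scoring is planned beside it.

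**What to change.** 1. On the concomitant-drug record already kept at each visit, add the clock time of every antipyretic dose and whether it was given for fever.
2. Pre-specify a second scoring of the same readings. Recovery is the first reading below 37.3℃ that starts 24 h with no reading at or above 37.3℃ and no antipyretic dose given for fever. The last condition keeps a dose taken for headache or myalgia from delaying recovery.
3. Report this scoring beside the current definition, and state before unblinding which of the two is primary. If the current one stays primary, declare that it counts recovery regardless of antipyretic use.
4. State that this changes scoring only. The rules on giving antipyretics (Concomitant) and on stopping study treatment (Discontinuation, and the closing sentence of Primary outcome measure) are unchanged.

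The cost is a few lines of endpoint text and two fields on an existing form. Under the antipyretic-aware scoring, recovery times will be somewhat longer and slightly more children will be censored.

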### Secondary Outcome measure

In clinical manifestation, we will record such as time point of fever subside, time point of disease alleviate, degree of disease remission and disappearance rate of individual symptoms;In laboratory examination, we will record the rate of negative conversion of Influenza viral;In treatment, we will record the usage and frequency of antipyretic and analgesic drugs;In outcome, we will record the incidence of complications of influenza.

### Criteria of comprehensive efficacy

Criteria of cure: the curative effect of clinical symptoms reaches the level of cure after finishing medication and the rapid detection for virus antigen of influenza turns negative. All two criteria must be met.

Criteria of invalid treatment: the curative effect of clinical symptoms is invalid, aggravated or complicated after the end of the medication and the rapid detection for virus antigen of influenza is still positive. Only one of the above is satisfied, it is considered invalid.

### Safety assessments

All participants will undergo the following laboratory examination. Safety assessments include vital signs, blood routine, urine routine, liver function, kidney function and twelve-lead electrocardiogram (ECG). We will judge anaphylaxis according to *criteria for diagnosis of anaphylaxis* by National Institute of Allergy and Infectious Diseases/Food Allergy and Anaphylaxis Network [29]. Then all adverse event (AE) will be judged in order to isolate ADR according to *Administrative Measures for the Reporting and Monitoring of Adverse Drug Reaction* [30] issued by the Drug Evaluation Center of the State Food and Drug Administration. And the Medical Dictionary for Regulatory Activities (MedDRA) will be used for standardization of ADR.

Assessment of study endpoints is shown in Table 2. It adheres to the Standard Protocol Items: Recommendations for Interventional Trials Statements (SPIRIT) [31].

**Table 2 Tab2:** Measurement items and assessment of study endpoints

Study period	Lead-in period	Treatment period				
**Follow-up times**	1	2	3	4	5	6
**Time point**	0 Day	24 h	48 h	72 h	96 h	120 h
**Case screening**						
History	√					
Indicator check	√	√				√
Basic information	√					
Determine the inclusion	√					
Informed content	√					
**Indicator check**						
Temperature	√	√	√	√	√	√
BP/HR/P/symptoms/signs	√	√	√	√	√	√
Blood routine/Urine routine	√					√
Liver function/Kidney function	√					√
Twelve-lead ECG	√					√
Pathogen test	√					√
Inflammatory factor test	√					√
**Others**						
randomization	√					
Drug distribution	√					
Drug recycle/ medication compliance						√
Combined medication		√	√	√	√	√
AEs		√	√	√	√	√
Recycle drug						√
**Conclusion of Completion of experiment**						√

### Data management

CRF will be written by researcher and that will be delivered to the specific data administrators to establish a database after passing the examination of the clinical supervisor. The data on CRF is inputted into the database by two independent data administrator respectively which is reviewed manually, checked by computer, examined blindly, and then is locked for the statistical analysis.

### Data statistic and analysis

#### Data selection

Four datasets will be conducted intention to treat (ITT), full analysis sets (FAS), per protocol set (PPS), and safety analysis set (SS). ITT is conducted for efficacy and AEs. FAS refers to the ideal set of participants who are as close as possible to the principle of intention to treat and is obtained after removing the participants from all the randomization with the least and reasonable method. PPS, a subset of FAS, is a data set generated from disease case set fully compliant with the trial protocol. SS refers to the randomized cases that have taken a tested drug at least once with safety evaluation data after treatment.

### Statistical method

Data analysis will be performed by professional statisticians using SAS 9.1.3. For measurement data, Group t test or Wilcoxon rank sum test will be used for comparison between groups; for counting data, χ^2^ test and Fisher exact test will be used, Rank sum test and Cochran Mantel Haenszel (CMH)test will used for grade data; for efficacy indicators, PPS analysis and FAS analysis will be used at the same time. The statistical analyses will use the two-sided hypothesis test. P ≤ 0.05 will be set as the significant level.

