## Method

### Study design

This is a randomized, double-blinded, double-dummy, parallel control of positive drug, multi-centre clinical study. The trial will be conducted in ten centers at China and collaborate with hospitals including Children’s Hospital Of Soochow University, Anhui Provincial Children’s Hospital, Qilu Children’s Hospital of Shandong University, Tianjin 4th Centre Hospital, Renmin Hospital of Wuhan University, Hebei Maternity&Child Healthcare Hospital, the Second Affiliated Hospital of Jiaxing University, the First Hospital of Hunan University of Chinese Medicine, Affiliated Hospital of Shanxi University of Traditional Chinese Medicine and one undetermined. The trial obtained ethical approval from Ethics Committee of The First Affiliated Hospital of Henan University of Chinese medicine (approval number: 2019HL-137-01), and will be conducted according to *the World Medical Association Declaration of Helsinki* and *Good Clinical Practice of Pharmaceutical Products* [20, 21].

Participants with influenza in Children will undergo a standardized baseline evaluation before treatment. All included participants are randomly divided into two groups: experimental group and control group.The experimental group receives RDN + Oseltamivir phosphate granule simulants and the control group receives Oseltamivir phosphate granules + RDN simulants. After five days of treatment with evaluation every 24 h, the efficacy and safety of two groups will be evaluated. The study design is shown in Fig. 1.

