### Exit criteria

Patients will leave the trial when one of the following criteria is met:

The symptoms of patients get worse after 3 days of medication;Some comorbidities, complications or special physiological changes occur during the test;Patients with poor compliance don’t reach 80% of the prescribed amount should be used in the trial;Cases breaking the blind or opening the blind urgently in the trial;Drugs out of prescribed protocol are used in the trial;Patients who want to quit the trial or refuse to accept prescription and examination have the right to withdraw from the trial according to the provisions of the informed consent. And the reason should be understood and documented possibly.

Notice: Whatever reason the cases are dropped out of the trial, the CRF should be kept and transformed into final result using the last result examined, and the efficacy and adverse reactions (ADRs) should be carried out using its full data set.

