### Discontinuation

Clinical symptoms and signs have no improvement or aggravation compared with those before enrollment after taking the medicine for 3 days or more. That needs to switch to another treatment and stop the medication. After completing the post-treatment evaluation and related laboratory tests, this case is declared over and this patient is recorded in PPS as invalid and qualified case statistics. When the body temperature of patient returns to normal and the symptoms and signs disappear within 5 days, the drug can be stopped. Follow-up visit is conducted after 24 h. If there is no recurrence, it will be counted as a recovered case.

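### The primary outcome is a time to event that some children will not reach, but the protocol analyses it as complete measurement data and carries the last result forward

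*Protocol article*

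**What the plan says.** All references are to the Protocol article.

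- **Endpoint (Primary outcome measure).** Recovery time is the "time when axillary temperature drops below 37.3℃ without repetition after the first use of the drug". The same section adds a confirmation window: "When axillary temperature drops below 37.3℃ without repetition in 24 h, it is the treatment end point".
- **Follow-up (Study design; Table 2).** Efficacy is judged "After five days of treatment with evaluation every 24 h", and the last scheduled visit is at 120 h.
- **Test (Statistical method).** "For measurement data, Group t test or Wilcoxon rank sum test will be used for comparison between groups". For the effectiveness analysis, Analysis contents says: "Measurement data uses covariance analysis which considering the central factor". No censoring rule and no time-to-event method is named.
- **Dropouts (Exit criteria).** For every dropout, regardless of cause, the rule is: "the CRF should be kept and transformed into final result using the last result examined". The same note keeps these children in the full data set when efficacy and safety are assessed.
- **Children stopped after three days or more without improvement (Discontinuation).** "this patient is recorded in PPS as invalid and qualified case statistics". No recovery time is assigned to them.
- **Expected loss (Sample size estimation and randomization).** A 20% dropout rate is allowed for.

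**The concern.** A child who leaves while febrile has a recovery time known only to be later than the exit. A t test, an ordinary Wilcoxon test and a covariance analysis all need a number for every child. The last-result rule is the only instruction on where that number comes from, and it does not suit a time. If the last observed hour is used, non-recovery is scored as recovery at that hour. If the last temperature is used, the recovery time is undefined.

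Some exits follow from the outcome itself (worsening, no improvement), so exit rates need not match between arms if the drugs differ in effect. This is the trial's only primary outcome. The error could create a difference that is not there or hide one that is.

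**Working it through.** **1. The plan's own figure.** The sample size confirms that recovery time is planned as a complete continuous variable. Inputs from the sample size section: 46.50 ± 1.74 h and 30.47 ± 1.69 h, and δ = 15.35 h. Two-sided 0.05 comes from Statistical method. Power is not stated; 80% is assumed. Pooled SD = √((1.74² + 1.69²)/2) = 1.715. Taking 15.35 h as a superiority margin:

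n = 2 × 1.715² × (1.960 + 0.842)² / (16.03 − 15.35)² ≈ 100 per group.

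This reproduces the stated 100, and 200 × 1.2 = 240.

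**2. How many children would carry a number without a recovery.** Assume 20% withdraw uniformly over 0–72 h. The share leaving before recovery is roughly 0.20 × mean/72:

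- mean 46.5 h: 0.20 × 46.5/72 = 12.9%
- mean 30.47 h: 0.20 × 30.47/72 = 8.5%

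Across Weibull shapes 1, 1.5 and 3, simulation gave about 13–16% and 8–10%.

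**3. Spread.** The documents give no usable SD for children, so a range is shown. If ±1.74 is a standard error with 54 per arm (an assumption: half of the 108 adults in the study cited in the Introduction), SD = 1.74 × √54 = 12.8 h. With 100 per arm it would be 17.4 h. The third value, 25 h, is simply assumed.

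**4. Type I error with exit time entered as recovery time.** Gamma-distributed times, mean 46.5 h in both arms, 120 per arm, follow-up to 120 h, 6,000 simulated trials per case in a check run for this write-up.

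| Scenario | SD 12.8 | SD 17.4 | SD 25 |
|---|---|---|---|
| Share febrile at 72 h | 3.6% | 8.4% | 14.7% |
| All febrile at 72 h coded 72 h, one arm only: t test | 5% | 7% | 15–16% |
| Same: Wilcoxon | 5% | 5% | 5–6% |
| 72 h coding in both arms: t test | 5% | 5% | 5% |
| Withdrawal 10% vs 30% over 0–72 h: t test | about 40% | about 30% | about 21% |
| Same: Wilcoxon | 32% | 28% | 22% |
| Same: log-rank, exits censored | 6% | 5% | 4% |

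The withdrawal rows can be checked by hand. While recovery times lie below 72 h, a withdrawing child loses on average (mean² + SD²)/(2 × 72) hours. At SD 12.8 that is (2162 + 164)/144 = 16.2 h, so a 20-point difference in withdrawal shifts the means by 0.20 × 16.2 = 3.2 h. The simulated shift was 3.3 h.

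With Weibull times (shapes 1, 1.5 and 3) the same 10% versus 30% scenario gave 13–29% for the t test, 11–25% for Wilcoxon and 4–6% for log-rank.

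**5. Equal exits.** With 20% versus 20% and no true difference, type I error was about 4–7% for all three tests. The mean in a 46.5 h arm fell to about 39–43 h; with exponential times, part of that fall comes from the 120 h limit.

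**6. The other direction.** With true means of 46.5 and 30.47 h, and 30% control versus 10% experimental withdrawal, the observed difference shrank from 16.0 h to about 9–12 h (Weibull).

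**7. What a log-rank analysis needs.** If times are exponential, HR = 46.50/30.47 = 1.53, and the required recoveries are 4 × (1.960 + 0.842)²/(ln 1.526)² = 176. At HR 1.5 the number is 191, at 1.4 it is 278, and at 1.3 it is 457.

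**The case against.** The strongest reply is that the harm depends on inputs the documents do not give. Day-3 exits depend on failure to improve; in a double-blind trial with identical recovery distributions both arms should exit alike, and then type I error stays near 5%. If ±1.74 h is a true SD, 72 h lies (72 − 46.5)/1.74 = 14.7 SDs above the mean and day-3 coding has no effect. Even at SD 12.8 h that scenario is negligible, and Wilcoxon is barely touched by it. All this stands. It does not cover unequal withdrawal for other reasons, or a real treatment difference, under which exits for failure will differ.

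Some stronger readings are tempting but unsupported:

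- *That the protocol enters exit time as recovery time.* It does not say so. That is the natural reading of a general carry-forward rule applied to a time.
- *That children still febrile at 120 h get a false time.* The rule covers dropouts only. For these children no value is stated at all.
- *That non-recovered children are dropped, with much larger bias.* The Exit criteria keep dropouts in the full data set, and Discontinuation keeps the non-improvers in the per-protocol set.
- *That three rival primary tests are declared.* Statistical method is a generic list by data type, and choosing between t and Wilcoxon is ordinary analysis-plan detail.
- *That only survival methods are valid.* A Wilcoxon test giving non-recovery the worst rank would also be defensible, but no such rule is stated.

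An unseen analysis plan could add censoring, but only by departing from the Exit criteria as written.

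**Conclusion.** The point holds as a misfit between stated rules and the endpoint: a time that some children will not reach is treated as complete, and the one rule for filling gaps either understates it or leaves it undefined. The size is conditional. It is nil to modest (about 5–16% type I error for the t test) when only children febrile at 72 h in one arm are affected. It is substantial (about 20–40% with gamma times, 11–29% with Weibull times) at 10% versus 30% early withdrawal. With equal exits and no true difference, type I error stays near 5%, with means that are too low. All figures assume a mean of 46.5 h, 120 per arm, and exit time entered as recovery time. The log-rank results also assume that withdrawal is unrelated to recovery. Few exits and near-complete recovery by 120 h would make the problem small, but the protocol's own 20% dropout allowance gives no ground for relying on that.

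**What to change.** 1. Exempt the primary outcome from the last-result rule in Exit criteria.
2. For this outcome, replace the t test, Wilcoxon and covariance analysis with Kaplan-Meier curves and a log-rank test stratified by centre, which is the randomisation stratum. Give the effect as a centre-stratified Cox hazard ratio or as restricted mean time to 120 h.
3. Count children stopped for worsening or no improvement, or still febrile at 120 h, as not recovered through 120 h. State how a first reading below 37.3℃ after 96 h is counted, since 24 h confirmation then runs past the last scheduled visit.
4. Censor other losses at the last temperature reading. Such censoring may be informative, so add a Wilcoxon sensitivity analysis with the worst rank for non-recovery.

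Adjustment beyond centre and temperature recording after exit are optional extras; the latter is new data collection.

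Cost: protocol and analysis-plan wording, slightly more analysis work, and a sample-size rationale restated in time-to-event terms. That restatement is not a formality. 240 children suffice for HR 1.53 if at least 176 recover, but the 278 recoveries needed at HR 1.4 exceed the planned enrolment. Treatment and exit rules are unchanged.
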